### Intervention

Patients will be randomized to ACL-R with either ST autograft (n = 100) or QT-B autograft (n = 100).

### Sample size calculation

To ensure adequate power, the sample size is based on Capio Artro Clinic’s clinical registry database from KT-1000 anterior knee laxity measurements available at the time of study planning, which indicated a standard deviation (SD) of 2.3 mm. This database includes over 7000 ACL-R and has served as the source to study postoperative knee laxity, functional test and graft comparisons [10–12, 30–32]. The power analysis is structured as follows: a 5% significance level, 80% power, and a minimum detectable difference of 1 mm in KT-1000 anterior knee laxity measurements. Based on these parameters, a minimum of 85 participants per group will be required as adequate sample. To account for potential dropouts, the sample size will be increased by 15%, resulting in 100 participants per group or 200 in total [33]. Recruitment will continue until each group has 100 fully evaluable participants for primary outcome measures.

### Randomization

In this single-center study, we will employ a simple 1:1 randomization to allocate participants to the two groups. The randomization process will be conducted by the independent researcher (not involved in the study) using randomizer.org, an online platform that generates random assignments. Participants will be randomized roughly one week after the patients sign the study consent form to participate in the study. Once included and randomized, the participants will fill out the baseline preoperative PROMs questionnaires. Given the inherently different graft harvesting sites, blinding of study participants, orthopedic surgeons as well as physiotherapist is not considered feasible. Participants will be informed of their allocation on the day of surgery, unless they explicitly requested to receive this information earlier. This approach was chosen to minimize potential cross-overs or withdrawals.

Although no stratification for sex will be performed, our aim is to have a balanced representation of sex that reflects the typical patient population for this condition at the clinic, with a distribution of 40% females and 60% males across both groups. This ratio also considers known differences in re-rupture risk and subjective outcome scores between sexes. Simple randomization in a RCT with 200 or more participants is well-suited as the likelihood of significant treatment imbalance is often negligible at these sample sizes [34]. All randomization procedures and study design elements are structured in accordance with CONSORT guidelines to ensure the highest standards of methodological transparency and rigor. Figure 1 shows the planned CONSORT flowchart.

**Fig. 1 Fig1:**
[figure not shown]
Planned CONSORT flow diagram for the randomised trial protocol

### Surgical procedures

All surgeries will be performed by one of four experienced surgeons (annual caseload > 50 ACL-R/revisions and total case history of > 500 ACL-R/revisions) [35], with vast experience using both ST and QT-B autografts. All surgeons were trained within the same clinic and follow a standardized institutional ACL reconstruction protocol. All patients will follow Capio Artro Clinic’s standardized anesthesia protocol and will be operated in a standard supine position. Patients will receive a preoperative antibiotic prophylaxis (2 g of Cloxacillin I.V.) which will be administered 30–45 min prior to surgery.

A standard diagnostic arthroscopy will be performed to map all the injuries. Meniscal pathology, including radial tears, ramp lesions, and root injuries, will be treated as clinically indicated with repair or resection depending on the type of injury and whether there are conditions for healing, and these procedures will not be considered exclusion criteria. Cartilage damage will be documented according to the International Cartilage Repair Society (ICRS) Classification [36] and handled according to the usual routine depending on size and depth. Superficial or minor cartilage injuries will be left while larger and deeper damaged cartilage will typically be drilled with a 1.6mm drill bit to stimulate cartilage regeneration that can cover the defect (microdrilling).

The harvest of the quadriceps tendon will be performed from a 5 cm long incision made from the middle of the patella to proximal. A full-thickness quadriceps tendon graft will be harvested from the middle section of the quadriceps tendon with a width of between 8–10 mm and with approximately 1 × 2 cm bone block from the proximal patella. The Tight Rope BTB I®(Arthrex®) will be used on the bone-block, and at the other tendinous end, two different non-reabsorbable sutures (either Ethibond® or Fiberwire®, size 2) will be sutured into the graft using baseball stitches.

The harvest of the semitendinosus tendon will be performed by using a 3–4 cm oblique incision over the pes anserinus. Using a Semitendinosus Tendon Stripper® (Arthrex®), the semitendinosus tendon will be harvested and will be four-folded. In case the graft volume is too small (< 8 mm), an additional gracilis tendon graft will be harvested and added according to the usual routine. The four-folded semitendinosus tendon graft will be looped over the Tight Rope I ® (Arthrex®) with Ethibond® size 5 and one non-reabsorbable sutures (either Ethibond® or Fiberwire®, size 2) into each of the two distal ends (free tails) of the ST graft using baseball stitching.

The selected autograft will be soaked in a sterile vancomycin solution (5mg/mL) prior to implantation during ACL-R to provide localized antibiotic prophylaxis. This technique aims to reduce the risk of postoperative infections by delivering high local concentrations of vancomycin directly to the graft and the knee joint [37–39].

In both groups, anatomical reconstruction of the ACL is performed with the accessory anteromedial portal in a in-side out technique through this portal the surgeon will use a 1.6 mm drill bit guide that will be placed and drilled in an anatomic position behind the lateral intercondylar ridge, approximately 60% of the anterior posterior width of the femur, toward the anterior medial (AM) bundle footprint, and later over-drilled to the same diameter as that of the graft. In the tibia, the tibia guide will be set at 50–55 degrees, depending on the patient anatomy, and once again a 1.6 drill bit guide will be drilled in the middle of the tibial ACL footprint, and over-drilled to the same diameter as that of the graft.

Both grafts used in this study will be fixed with Milagro® interference screw in the tibia with at least 1 mm oversized compared to the graft. Fixation distally in the tibia occurs in the degree of flexion that the surgeon decides optimal for graft isometry throughout the whole range of motion (ROM) of the knee.

Lateral extra-articular tenodesis (LET) procedures will not be performed in this cohort. Individuals with generalized joint hypermobility (Beighton score ≥ 5), who may have been considered for LET, will be excluded.

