Interestingly, the quadriceps tendon (QT) autografts yields comparable clinical and functional outcomes to both HT and BPTB autografts but with certain unique advantages [13, 14]. Notably, QT autografts have been associated with reduced incidence of anterior knee pain and kneeling discomfort compared to BPTB grafts, two common complaints after ACL-R with BPTB grafts [15, 16]. Moreover, QT autografts might offer the lowest donor-site morbidity among the three autografts (HT, BPTB and QT grafts), making it an interesting option to use [17].

The quadriceps tendon (QT) can be harvested either as an all–soft tissue graft (QT-S) or with a patellar bone block (QT-B). QT-B offers the theoretical advantage of bone-to-bone healing, potentially improving graft incorporation and stability, although there is a risk of complications such as patellar fracture. In contrast, QT-S avoids bone harvest and may be more suitable in certain patient groups, such as skeletally immature individuals [18, 19]. Recent systematic reviews and registry studies have reported comparable clinical outcomes between QT-B and QT-S [18, 19], although QT-B remains the more frequently studied QT autograft [20].

High quality registry studies have also provided conflicting evidence on whether QT grafts are associated with higher revision rates. In the Danish Knee Ligament Reconstruction Registry there have been reports that the revision rate for QT autografts was higher than that for HT and BPTB grafts; however, these findings have later been shown to only implicate cases where surgeons with less experience using the QT autografts have performed the ACL-R, emphasizing the importance of surgical expertise and proper technique in achieving optimal outcomes [21, 22].

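### The primary laxity comparison names no surgeon term, although four unblinded surgeons operate and allocation is not stratified by surgeon

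*Protocol article*

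**What the plan says.** Under Surgical procedures, the protocol states: "All surgeries will be performed by one of four experienced surgeons (annual caseload > 50 ACL-R/revisions and total case history of > 500 ACL-R/revisions"). The same sentence says that the four have extensive experience with both grafts, and the next says that they trained in one clinic and follow one institutional technique. One step is left to judgement: "Fixation distally in the tibia occurs in the degree of flexion that the surgeon decides optimal for graft isometry".

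Randomization: allocation is simple 1:1, done about a week after consent and so before surgery. No stratification by surgeon is described, and "blinding of study participants, orthopedic surgeons as well as physiotherapist is not considered feasible". Nothing in the article says how or when a patient is given an operating surgeon.

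Background, on higher registry revision rates with quadriceps tendon grafts: "these findings have later been shown to only implicate cases where surgeons with less experience using the QT autografts have performed the ACL-R".

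Statistical analysis: laxity is compared between groups with a variance-based test, to be chosen after data collection. Adjustment for baseline values is an optional secondary analysis. The Discussion adds that important covariates will be adjusted for if baseline imbalance is seen. Surgeon is named in neither place.

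**The concern.** In a surgical trial the operator can influence the result, and the protocol accepts this for the graft under study. If patients were listed with a surgeon once their graft was known, randomization would no longer balance surgeons between arms. A difference between surgeons in mean laxity would then appear as a difference between grafts, or would hide one. The second possibility matters because the stated hypothesis is that there is no difference.

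The plan's adjustment rule does not reliably cover this. It depends on imbalance observed at baseline, and a surgeon assigned after allocation is not a baseline characteristic. A decision to adjust that waits for the data is also weaker than one made in advance.

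**Working it through.** **Inputs from the protocol (Sample size calculation).** The design uses "a 5% significance level, 80% power, and a minimum detectable difference of 1 mm in KT-1000 anterior knee laxity measurements", and registry data "which indicated a standard deviation (SD) of 2.3 mm". The stated result is that "a minimum of 85 participants per group will be required as adequate sample", and then that "the sample size will be increased by 15%, resulting in 100 participants per group or 200 in total".

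**Reproducing the plan's figure.** n per group = 2 × (1.960 + 0.842)² × 2.3² / 1² = 83.0, rounded up to 84. The t-based solution is 84.01, rounded up to 85. Then 85 / (1 − 0.15) = 100. The stated 85 and 100 reproduce with a two-sided test. The present point does not affect them.

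**Standard error of the graft contrast.** 2.3 × √(2/100) = 0.325 mm.

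**Case A: surgeon independent of allocation.** Only chance imbalance remains. If each surgeon does a quarter of the cases, the between-arm difference in one surgeon's share has SD √(2 × 0.25 × 0.75 / 100) = 0.061, or about 6 points. The documents give no between-surgeon variance, so it was assumed to be 1% to 10% of the total. That is a surgeon SD of 2.3 × √0.01 = 0.23 mm to 2.3 × √0.10 = 0.73 mm. A simulation with four surgeons, 100 patients per arm, no graft effect, an unadjusted two-sample test and 8,000 runs per setting gave a type I error of 4.7% to 5.0%. The SD of the surgeon-induced shift was 0.03 to 0.09 mm. A surgeon term would multiply the standard error by about √0.99 to √0.90, taking it from 0.325 to between 0.324 and 0.309 mm. That is a gain of 0.5% to 5%.

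**Case B: surgeon assigned according to graft.** Bias = (difference in surgeon share between arms) × (difference in mean laxity between that surgeon and the others). Assume one surgeon does 40% of one arm and 10% of the other, and differs by 0.5 to 1.0 mm:

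- 0.30 × 0.5 = 0.15 mm. Standardised shift 0.15 / 0.325 = 0.46, rejection probability 7.5%.
- 0.30 × 1.0 = 0.30 mm. Standardised shift 0.30 / 0.325 = 0.92, rejection probability 15.2%.

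Against the 1 mm target these are 15% and 30%. In the other direction, a true 1 mm difference offset by 0.30 mm lowers power at 100 per group from Φ(1/0.325 − 1.96) = 87% to Φ(0.7/0.325 − 1.96) = 58%.

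The simulation with surgeon linked to arm, over the same assumed variance range, gave:

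| Share of two surgeons, one arm / other arm | Type I error | SD of shift |
|---|---|---|
| 50% / 50% (Case A) | 4.7–5.0% | 0.03–0.09 mm |
| 60% / 40% | 5.5–7.5% | 0.05–0.17 mm |
| 80% / 20% | 6.5–24% | 0.14–0.44 mm |

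A 30-point gap in one surgeon's share is about 0.30 / 0.061 = 4.9 chance SDs. Case B therefore needs systematic assignment by graft and would not arise by luck.

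**The case against.** The strongest reply is that the article is silent on surgeon assignment, and that theatre listing and model covariates may be settled in the full protocol or an analysis plan not shown here. That stands in part. What remains is what the article does state: a group comparison without surgeon, and adjustment that is optional or triggered by imbalance.

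The second reply is that the operator-experience passage concerns registry revision rates and not KT-1000 laxity at 6 months. It adds that the protocol answers the passage with surgeons experienced in both grafts and trained together. This also stands in part. The numerical caseload threshold counts all ACL reconstructions and gives no figure for the quadriceps graft, but the protocol does assert that experience for all four surgeons.

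Three stronger readings are tempting, and the documents do not support them:

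- A reader might infer that the surgeon is chosen after allocation. No passage says so. If the surgeon is fixed first, randomization protects the comparison.
- A reader might infer that a chance imbalance in surgeons biases the test. It does not. Case A shows type I error near 5%, because the standard error already covers that variation.
- A reader might infer that the surgeon-chosen flexion angle contradicts the standardised technique. The same rule applies to both arms, and a standard technique can contain a patient-specific step. The angle could carry surgeon differences into the graft contrast only if surgeons were unevenly split by graft.

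**Conclusion.** The concern holds in a limited form. The stated primary comparison omits surgeon, and the stated adjustment rules would not dependably bring it in. Four unblinded surgeons operate after an allocation that is not stratified by surgeon. Confounding of graft with surgeon is possible but not shown.

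The size depends on a fact the article does not give. If the surgeon is independent of allocation, the loss is only a little precision. If assignment followed the graft, a bias of 0.15 to 0.30 mm and a false-positive rate of about 7% to 15% illustrate what could happen. Those figures rest entirely on the assumed surgeon shares and between-surgeon differences, and neither comes from the documents. The sample size is unaffected. The point is worth acting on because the remedy is nearly free and the 6-month analysis is not expected before the second half of 2026.

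**What to change.** - Pre-specify operating surgeon (four levels) as a fixed factor in the primary laxity model, whatever balance is observed. Surgeon should already be in the operative record, so this covers every patient, including those already treated.
- Tabulate surgeon by arm, and report the graft difference within each surgeon descriptively, without a test-based claim.
- State how and when the operating surgeon has been assigned so far. If it was always before allocation, one sentence settles the question of confounding.
- For the remaining patients, record the surgeon before the allocation is released, and log any change with its reason. With 170 of 200 recruited at the time of writing, this reaches about 30 patients (15%). The model term is therefore the main remedy.

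The cost is three degrees of freedom out of about 200 and slightly less flexible theatre scheduling. The surgeon term has one limit: it removes differences in surgeons' average results, but not any selection of particular patients to particular surgeons after allocation. The table by arm and the log of changes are there to show whether that occurred.

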### Postoperative rehabilitation

For both surgical procedures (ACL-R with ST or QT-B grafts), patients will be followed by a physiotherapist that will follow the standardized rehabilitations protocols from the clinic and individualize the rehabilitation when needed for the specific patient. Participants will be allowed to fully weight bear the knee with the aid of crutches postoperatively in the event of isolated ACL-R and in ACL-R with meniscal resection, meniscal ramp lesion repair or meniscal bucket-handle repair. Individuals undergoing meniscal root repair will be allowed to partially weight bear for 6 weeks and those undergoing a repaired radial meniscal lesion will be instructed not to weight bear during the first 6 weeks. ROM will be restricted for all meniscal repair procedures initially to protect the meniscus early in the healing process. Surgically treated cartilage defects in the femuro-patellar region will be allowed to weight bear in the ROM restricted at 0–30 degrees with a knee orthosis, while surgically treated cartilage defects in the tibiofemoral region will be treated with partial weight bearing for 6 weeks. Postoperative weight-bearing and ROM restrictions will not be used as stratification variables, and no subgroup analyses will be performed based on these factors.

According to the standardized rehabilitation protocol, the rehabilitation progression follows a structured, criterion-based protocol rather than a purely time-based schedule. After the initial six weeks, patients transition through defined phases focusing on strength development, neuromuscular control, and functional capacity. From week 13–14 onward, there will be no restrictions on quadriceps training. Clearance to begin impact activities such as running will typically occur around 4 to 5 months postoperatively and requires ≥ 80% limb symmetry index (LSI) in quadriceps and hamstring strength, along with resolution of joint effusion. Return to sport (RTS) is generally assessed between 8 and 12 months and requires ≥ 90% LSI in both strength and hop testing, absence of swelling or functional complaints, and adequate movement quality during sport-specific tasks. Although adherence to the rehabilitation program will not be tracked, all functional tests are performed at standardized checkpoints using validated protocols to assess progression (Table 1). Tailoring of the rehabilitation program will be allowed based on the individual recovery and sport-specific demands.

**Table 1 Tab1:**
[figure not shown]
Scheduled follow-up and assessment of primary and secondary outcomes

### Outcomes

The rationale behind the outcome measurement in this study is to evaluate the patients knee laxity at 6 months, subjective knee function through PROMs, as well as other physical and objective outcomes. The exact time points of the different outcome measurements during the outpatient follow up are summarized in Table 1.

### Primary outcome

#### Knee Laxity at 6 months post ACL-R

Knee Laxity will be measured preoperatively and at 6 months postoperatively using the KT-1000 arthrometer® (MEDmetric®, Corp, San Diego, CA, USA) in accordance with the clinic’s standard routine for postoperative evaluation of ACL-R [10]. Patients will be positioned supine with the knee at approximately 20 degrees of flexion with the help of a bolster placed under the thighs, and with the feet are supported on a footrest to minimize muscle contraction and prevent external rotation. The contralateral (uninjured) knee will be tested first, followed by the ACL-injured knee. For each knee, three trials will be conducted using the standardized anterior force corresponding to 134 N (third audible “click” of the KT-1000). Between trials, the arthrometer will be recalibrated and the median value of the three valid measurements will be recorded for each side. The STS difference in ATT between the ACL-injured knee and the healthy contralateral knee (measured preoperative to postoperative) will be expressed in millimeters. To reduce inter-rater variability, all measurements will be performed by two unblinded, experienced physiotherapists, each with over 10 years of experience in arthrometric laxity assessment following ACL injury and reconstruction.

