**Methods:**

This is a single center RCT. Two Hundred ACL-R patients aged 16–40 years with a Tegner Activity Scale (TAS) of ≥ 7 prior to the ACL injury will be randomized to receive either a ST graft or a QT-B graft at the time of ACL-R. All participants will receive standard postoperative care and rehabilitation, followed by comprehensive follow-up. The primary outcome was the side-to-side (STS) difference in anterior tibial translation (ATT) at 6 months. Secondary outcomes include patient-reported outcome measures (PROMs), isokinetic strength testing, imaging-based graft evaluation, surgical and clinical events, and 10-year radiographic evidence of joint degeneration. Detailed definitions and timepoints are provided in the full manuscript (Table 1).

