## Methods

### Objectives

The primary aim of this study is to investigate potential differences in STS knee laxity at 6 months after ACL-R performed with either a ST graft or a QT-B graft in athletes with Tegner Activity Scale (TAS) ≥ 7 [29]. Patients will be followed for 6 months post ACL-R for the primary endpoint. Various secondary outcomes will also be measured to enable comprehensive evaluation of both short- and long-term outcomes.

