### Hypothesis

For primary outcomes, it is hypothesized that 1) there will not be any significant differences in STS knee laxity at 6 months.

Further, for secondary outcome, it is hypothesized that 2) deficits in the isokinetic knee extension and flexion strength will differ between the choice of graft, 3) no differences in hop test LSIs will be observed, 4) no differences in frequently used PROMs after ACL-R will be noted, 5) no differences in return to sports rates, 6) nor differences in graft site morbidity will be seen.

Finally, it is hypothesized that 7) no differences in graft failure or contralateral ACL rupture will be observed, and that 8) the incidence of radiographic or symptomatic (PROMs) osteoarthritis at 10 years will be similar across both grafts.

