### Participants

The study will take place at the Capio Artro Clinic, Stockholm, Sweden, a highly specialized orthopedic clinic performing over 1000 ACL-Rs annually. The recruitment of the study participants will be performed at the outpatient department once inclusion and exclusion criteria have been checked. The TAS level will be assessed by the orthopedic surgeon responsible for patient enrolment into the study. The patients meeting inclusion criteria will be informed about the study and will be asked to participate. During the outpatient visit they will be handed the written consent form by the orthopedic surgeon and will later be randomized by an independent researcher, not directly involved in the study. All participants will undergo a standardized preoperative rehabilitation program prior to ACL-R. Data collection for the primary outcome will continue for two years.

Inclusion criteria:Age 16 −40 yearsPre-injury TAS ≥ 7Intended return to sports to prior sport and TAS LevelTime between injury and inclusion not more than 6 monthsMR verified ACL rupture

Exclusion criteria:Previous knee injury with symptoms before ACL injuryNeurological disease, inflammatory disease, connective tissue disease or balance disorderPrevious lower limb fracture or surgeryLaxity in the medial collateral ligament (MCL) and lateral collateral ligament (LCL) < grad 1Posterior cruciate ligament (PCL) rupture or Multiligament knee injury (MLKI)Radiographic sign of osteoarthritis (OA)Previous knee surgery or ligament injury in contralateral kneeBeighton score ≥ 5

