#### Statistical analysis

The statistical analysis will be conducted using SPSS software (version 29.0 or updated version). Descriptive statistics, including frequency, mean, and standard deviation, will be computed for all variables, and normal distributions will be assessed using histograms, Q-Q plots and Kolmogrov-Smirinov test. Continuous variables will be compared using parametric or non-parametric methods, depending on data distribution. Categorical variables will be analysed using Pearson’s chi-square test or Fisher’s exact test.

For anterior knee laxity measurements (KT-1000), mean ± standard deviation and median (range) values will be reported. A variance-based statistical test will be used to compare, preoperative and postoperative anterior knee laxity, as well as ATT reduction between treatment groups. The choice of test will be determined based on the distribution and characteristics of the data after collection. Adjustments for baseline values may be included as part of a secondary analysis to ensure robust comparisons.

Postoperative STS values in knee laxity will be categorized and presented in three groups according to the IKDC form: Normal ≤ 2 mm (A), nearly normal 3–5 mm (B), and abnormal > 5 mm (C and D) [10, 11, 56]. The postoperative side-to-side (STS) difference will be dichotomized as either normal (≤ 5 mm) or failure (> 5 mm). Distributions and proportions of failures will be compared between intervention groups using Pearson’s chi-square test.

The study will employ both intention-to-treat (ITT), and per-protocol (PP) to ensure robust assessment of outcomes for each surgical group. The ITT analysis will include all randomized patients in their originally assigned groups, regardless of any protocol deviations or dropouts. Missing data for the ITT analysis will be managed using imputation methods where necessary. The PP analysis will include only those patients who fully adhered to the study protocol, completing their assigned surgery and primary outcome assessments.

Secondary outcomes will be evaluated across follow-up timepoints (Table 1). Continuous outcomes will be analyzed using a variance-based statistical test to assess within-group changes over time. Adjustments for baseline values may be included as part of a secondary analysis to ensure robust comparisons. Individual time points will be assessed using independent samples t-tests or non-parametric test, depending on the distribution of the data.

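### The primary laxity variable is stated both as the 6-month side-to-side difference and as a preoperative-to-postoperative difference, and the protocol does not say which of them the 2.3 mm SD and 80% power describe

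*Protocol article*

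**What the plan says.** All quotations are from the protocol article.

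- Abstract, Methods: "The primary outcome was the side-to-side (STS) difference in anterior tibial translation (ATT) at 6 months".
- Objectives: "The primary aim of this study is to investigate potential differences in STS knee laxity at 6 months after ACL-R", followed by "Patients will be followed for 6 months post ACL-R for the primary endpoint".
- Hypothesis: "there will not be any significant differences in STS knee laxity at 6 months".
- Primary outcome, under a heading that names 6 months: "The STS difference in ATT between the ACL-injured knee and the healthy contralateral knee (measured preoperative to postoperative) will be expressed in millimeters". The same paragraph places KT-1000 testing preoperatively and at 6 months, by two unblinded physiotherapists.
- Statistical analysis: a variance-based test will "compare, preoperative and postoperative anterior knee laxity, as well as ATT reduction between treatment groups". The test is to be chosen once the data are in, and adjustment for baseline is something that may be done in a secondary analysis.
- Participants: "Data collection for the primary outcome will continue for two years".
- Sample size calculation: the basis is "KT-1000 anterior knee laxity measurements available at the time of study planning, which indicated a standard deviation (SD) of 2.3 mm", with a 1 mm difference, 5% significance and 80% power. This gives 85 per group, raised to 100, and recruitment continues until each group has 100 evaluable for the primary outcome.

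**The concern.** A 6-month STS value and a preoperative-to-postoperative change in STS are different variables. Under randomisation both between-group contrasts have the same expected value, because the graft cannot affect preoperative laxity. They differ in variance, in the estimate obtained in any one sample, and in the p-value. One may be significant when the other is not.

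Two things follow. First, a sample size built on one SD is verified only for the variable with that SD. Second, the variable, the test and the use of baseline are all left open while the outcome is measured by assessors who know the allocation. The contrast reported as primary could then be settled after the results are seen. The sentence about two years adds a third uncertainty, over when primary data collection ends.

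**Working it through.** **1. The plan's own figure.** Inputs from the sample size section: difference 1 mm, SD 2.3 mm, 5% significance (two-sided assumed), 80% power.

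n per group = 2 × (1.960 + 0.842)² × 2.3² / 1² = 83.04, so 84. The t-test version gives 84.01, so 85. The stated 85 reproduces. A one-sided test would need 66 and does not match. Dropout: 85 / (1 − 0.15) = 100, as stated. The t-test power for a variable with SD 2.3 mm is 80.5% at 85 per group and 86.4% at 100.

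**2. Power if the variable is the change.** The documents give neither the pre-post correlation r nor a preoperative SD. Assume that 2.3 mm is the 6-month SD and that the preoperative SD is equal. Then

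SD of change = 2.3 × √(2(1 − r)).

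For example, r = 0.2 gives 2.3 × √1.6 = 2.91 mm.

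| r | SD of change (mm) | Power, 85 per group | Power, 100 per group |
|---|---|---|---|
| 0 | 3.25 | 51% | 58% |
| 0.2 | 2.91 | 61% | 68% |
| 0.4 | 2.52 | 73% | 80% |
| 0.5 | 2.30 | 80% | 86% |
| 0.6 | 2.06 | 88% | 93% |
| 0.7 | 1.78 | 95% | 98% |

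The break-even r for 80% power is about 0.49 at 85 per group and 0.40 at 100 (normal approximation). Above r = 0.5 the change has more power than the 6-month value. A larger preoperative SD lowers the figures: with an assumed 3.0 mm and r = 0.3, the SD of change is √(2.3² + 3.0² − 2 × 0.3 × 2.3 × 3.0) = 3.19 mm, and power is 53% at 85 per group. If 2.3 mm is already the SD of the change, power for the change is the planned 80%.

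**3. Cost of leaving both contrasts open.** With equal SDs, the correlation between the 6-month value and the change is √((1 − r)/2): 0.71 at r = 0 and 0.39 at r = 0.7. With no true difference, the chance that at least one of two 5% two-sided tests is significant (bivariate normal) is 8.3% at r = 0, 8.6% at 0.2, 8.9% at 0.4 and 9.4% at 0.7.

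**4. The two-year sentence.** Read as follow-up per patient, it conflicts with the 6 months in the Objectives. Read as a calendar period, it does not fit the Trial status section, where the first participant was included in February 2020, inclusion is expected to end in late 2025 or early 2026, and the 6-month analysis follows in the second half of 2026 or early 2027.

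**The case against.** The strongest reply is that the 6-month time point is used almost throughout: in the abstract, aim, hypothesis, outcome heading, discussion and trial status. On that view the parenthesis only states loosely when STS is measured, since the paragraph opens by naming both occasions and defines no subtraction. The statistical section lists comparisons without redefining the outcome, and ranking them may be left to an analysis plan that is not shown. Part of this stands: the time point is not in serious doubt, and the intended variable is probably the 6-month value. But the parenthesis sits in the operative definition, where its plain sense is a change, and ATT reduction then appears beside postoperative laxity with no label. An analysis plan would have to depart from one of these statements.

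Three stronger readings are tempting and are not supported.

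- A reader might infer that the 80% power holds only for the 6-month value. The protocol does not say which variable has the 2.3 mm SD and gives no correlation, and showing only low values of r would be selective.
- A reader might count four competing definitions. ATT reduction is probably the same quantity as the preoperative-to-postoperative difference, and the two-year sentence names no laxity endpoint at two years. There are two candidate variables and one timing conflict.
- A reader might infer that the trial will claim success on whichever contrast is significant. No such rule is stated. The 8.3% to 9.4% is what an unexcluded choice would cost.

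The full assessment schedule (Table 1) is not visible, so the KT-1000 timing rests on the outcome text alone.

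**Conclusion.** The point holds as an inconsistency in the definition of the primary variable, made worse by an analysis section that fixes neither the contrast, the test nor the use of baseline. It does not hold as a demonstrated shortage of power. The stated power is correct for a variable with SD 2.3 mm. For the change it could lie anywhere from 51% to 95% at 85 per group, or 58% to 98% at the 100 evaluable per group that the protocol promises, for r from 0 to 0.7. Those ranges assume that 2.3 mm is the 6-month SD and that the preoperative SD equals it. The false-positive figure of about 8.3% to 9.4% makes the same equal-SD assumption and applies only if either contrast could be claimed. The point deserves correction before the primary analysis because outcome assessment is unblinded and the correction is nearly free.

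**What to change.** - Name the STS difference at 6 months (operated minus contralateral knee, in mm) as the sole primary variable in every section.
- Remove or clarify the parenthesis in the outcome definition.
- Analyse that variable with the preoperative STS value as a prespecified covariate, in place of the optional secondary adjustment. With equal SDs the residual SD is 2.3 × √(1 − r²), which never exceeds 2.3 mm, so the planned power is essentially preserved if 2.3 mm is the 6-month SD.
- Label ATT reduction as secondary and report preoperative laxity descriptively.
- State in the sample size section which variable the 2.3 mm SD describes.
- Reconcile the two-year sentence with the 6-month endpoint and the recruitment dates.

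The cost is wording in a few places. Preoperative KT-1000 is already being measured, so no new data are needed. With 170 participants recruited when the article was written and the 6-month analysis expected no earlier than the second half of 2026, the change can be made and dated before the primary analysis.
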